#### Outcomes: cost-effectiveness

3.6.3

To consider the social value generated by the initiative, a triple bottom line of social, economic and environmental value through Social Returns on Investment (SROI) will be considered (74). Economic evaluation is a tool used to guide resource allocation decisions in health care, where effects are often expressed in health-related units. However, it is anticipated that interventions that alleviate loneliness are not only associated with health benefits but also broader societal benefits, where benefits often accrue across sectors. As such, a broader evaluation framework is required to determine the social and economic value of the *Connect Local* intervention, such as Social Return on Investment (47).

The scope of the health economic evaluation will involve data collected as part of this evaluation between May 2023 and May 2025 (8 quarters), during which time the program will be fully established and running in the target LGA. The categories of stakeholders that will be operationalised will be:

Beneficiaries: those who experience the outcomes of an intervention (community members) involved in *Connect Local*;Implementers: suppliers and subcontractors (Bolton Clarke, Social Service providers);Promoters: those who provide support and a conducive environment for implementation of the intervention (health care providers); andFunders: those who directly and indirectly finance the project (The Ian Potter Foundation, Department of Health, target LGA City Council).

The theory of change, shown in Figure 3, developed for this study, was used to underpin this cost-effectiveness evaluation.

The evaluation component will involve the following SROI process steps:

##### Evidencing outcomes and giving them a value

3.6.3.1

Data on loneliness, social connection, depressive symptoms, wellbeing, quality of life and health service use at baseline, 3, 6 and 12 months will provide evidence of outcomes, drawing comparisons between the intervention and comparator groups. Each outcome will be then monetised using financial proxies. Costs and benefits that occur at different time points will be made comparable by adjusting for inflation in order to calculate net present value (47).

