### Program cost-effectiveness

3.2

(i) Among the target cohort within the study LGA, *Connect Local* will generate improvements in the health, wellbeing, and quality of life of participants that can be translated into monetary values. This will be established by comparing the situation before and after the *Connect Local* intervention and comparing outcomes with the comparator group.(ii) When comparing the cost of the intervention with the social and economic outcomes, including health service utilisation, the SROI ratio will yield a return greater than the investment.

*Research question using PICO:*

Is *Connect Local* more cost effective to address loneliness, social isolation, depressive symptoms and wellbeing in older community members compared to no *Connect Local*?

A proposition is proposed for the third research component:

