##### Calculating the SROI

3.6.3.3

This will involve adding up all benefits. Investment into the *Connect Local* will be compared to the discounted, monetised value of benefits. The discounted, monetised value of benefits and outcomes will be divided by total investment (inputs) to estimate the SROI ratio.

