**BOX 1 Tools used to calculate Social Return on Investment (SROI)**

**Tools of SROI**
Establishing impact (attribution, deadweight, displacement, drop-off):To minimise the risk of overclaiming the benefits it was necessary to account for deadweight, displacement, attribution, and attrition.*Deadweight:* responds to the question: ‘How much of the outcome would still be attained without the activity delivered?’We will use the quantitative data captured in the comparator group to ascertain this information, measured as a percentage, and then that percentage of the outcome will be deducted from the total quantity of the outcome.*Displacement* responds to the question: ‘Were there any activities with the same outcome displaced by the intervention being evaluated?’We will capture this information when collecting service information from participants involved in the program and comparing them to what was captured in the comparator group – using a percentage and deducted from the total outcomes.*Attribution* responds to the question; ‘Who else contributed to the attainment of the outcome?The research team will identify all relevant stakeholders and to assess how much of each outcome could be attributed to the delivery of Connecting Communities to Care with due circumspection. This will be calculated as a percentage.*Drop-off* responds to the question: ‘How much of the outcome is lost in the years post intervention?’To calculate the percentage of the outcome lost in the years after delivery of the intervention. It is calculated by deducting a fixed percentage from the remaining level of outcome at the end of each year. This will be calculated as a percentage.

*Calculating the SROI:*

The calculation of the SROI will consider the total value of the inputs in the program. The discounted, monetised value of benefits and outcomes will be divided by total investment (inputs) to estimate the SROI ratio.

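### Section 3.6.3.1 treats inflation adjustment as the route to net present value, so the SROI ratio has no stated time discounting and later-year benefits are modestly overstated

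*Protocol article*

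**What the plan says.** The economic hypothesis in section 3.2(ii) is that "the SROI ratio will yield a return greater than the investment", in other words that the ratio exceeds 1. The steps towards that ratio are spread over several places in the protocol article.

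- **Time adjustment (3.6.3.1):** "Costs and benefits that occur at different time points will be made comparable by adjusting for inflation in order to calculate net present value". No discount rate is given there or elsewhere.
- **Deductions (3.6.3.2):** monetised outcomes are 'discounted' for deadweight, displacement, attribution and drop-off. Section 3.6.3.3 and Box 1 then divide the 'discounted' benefits by total inputs.
- **Later years (Box 1):** drop-off removes a fixed percentage of the remaining outcome at the end of each year after delivery. The number of years is not stated. Data collection for the economic evaluation covers May 2023 to May 2025 (3.6.3).
- **Valuation and summing:** the evidence is "Data on loneliness, social connection, depressive symptoms, wellbeing, quality of life and health service use at baseline, 3, 6 and 12 months". Section 3.6.3.1 adds "Each outcome will be then monetised using financial proxies", and 3.6.3.3 says "This will involve adding up all benefits".
- **Use of the comparator:** section 3.2(i) combines a before-after comparison with "comparing outcomes with the comparator group". Section 3.6.3.1 evidences outcomes by "drawing comparisons between the intervention and comparator groups". For deadweight, Box 1 says "We will use the quantitative data captured in the comparator group to ascertain this information, measured as a percentage", and that share is deducted from the total quantity of the outcome.

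**The concern.** Price adjustment and discounting are separate operations. The first removes the effect of general price change, so that sums from different years are in the same money. The second allows for a benefit received later being worth less today than the same real benefit received now. Doing only the first is the same as discounting at a real rate of zero. The sentence in 3.6.3.1 presents the first operation as sufficient for net present value, so this is a step stated wrongly rather than a detail left out.

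The error runs in one direction. Investment comes early and projected benefits come later, so omitting discounting raises the ratio. The ratio is the test of a formal hypothesis, and the Discussion offers the SROI result to decision makers as a basis for allocating resources and replicating the program.

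Two secondary matters affect the same ratio. Sections 1.2 and 2.1 describe the outcomes as a chain, in which less loneliness, isolation and depression lead to better wellbeing and then to less health service use. Valuing every link and adding them may count part of one gain more than once. And Box 1 does not say whether the quantity from which deadweight is deducted is the gross before-after change or a difference already taken against the comparator.

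**Working it through.** The documents give no SROI ratio, proxy value, discount rate, deadweight percentage or projection period, so there is no figure of the plan's own to reproduce. The sizes below are illustrations.

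**1. Is time discounting stated under another name?** Section 3.6.3.2 attaches the word 'discounted' to four deductions, none of which concerns time preference. Drop-off is the nearest, but it describes the outcome itself fading, not the lower present value of what remains. Section 3.6.3.3 reuses the word straight afterwards for the numerator of the ratio. The only statement about timing is the inflation sentence in 3.6.3.1.

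**2. Size of the omission.** Let the yearly benefit in constant prices be b_t = (1 − drop-off)^t for t = 0, …, T − 1. The overstatement is

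sum of b_t ÷ sum of b_t/(1 + r)^m − 1,

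with m = t + 1 if benefits fall at year end and m = t if they fall at the start of the year. Assumptions: r = 3%, 5% or 7%; all costs at time 0; yearly drop-off from 0 to 50%; T = 1, 2 or 5.

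| Horizon | Largest case: no drop-off, year end (3% / 5% / 7%) | Smallest case: 50% drop-off, start of year (3% / 5% / 7%) |
|---|---|---|
| 1 year | 3.0% / 5.0% / 7.0% | 0% / 0% / 0% |
| 2 years | 4.5% / 7.6% / 10.6% | 1.0% / 1.6% / 2.2% |
| 5 years | 9.2% / 15.5% / 21.9% | 2.5% / 4.0% / 5.6% |

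Worked example, two years at 7%, no drop-off, year end: 2 ÷ (1/1.07 + 1/1.07²) = 2 ÷ (0.9346 + 0.8734) = 2 ÷ 1.8080 = 1.106. The zero entries for one year are the limiting case in which benefits and costs coincide in time. If costs are spread over the program they would be discounted too, and the overstatement would be smaller than shown.

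**3. What this means for the threshold.** If benefits are overstated by a fraction x, the discounted ratio is the reported ratio ÷ (1 + x). In the largest cases above, only a reported ratio between 1 and about 1.11 (two years) or 1 and about 1.22 (five years) would fall to 1 or below. Nothing in the documents indicates where the ratio will lie.

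**4. Overlap between outcomes.** Suppose six equally valued outcomes, with a share s of each one after the first already counted. The overstatement is 6 ÷ (1 + 5(1 − s)) − 1: 9% at s = 0.10 (6/5.5), 26% at s = 0.25 (6/4.75) and 71% at s = 0.50 (6/3.5). All of these shares are assumed, and the documents support none in particular. None of the deductions in Box 1 removes value shared between outcomes.

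**5. Base for deadweight.** Let the comparator change be a share c of the intervention-group change. Taken once from the gross change, the deduction leaves 1 − c. Applied to a between-group difference, it would leave (1 − c)². At c = 0.3 (assumed) that is 0.70 against 0.49. The first is correct; the second would understate the benefit.

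**The case against.** The strongest reply is that this is a wording slip in a condensed article. The sentence names net present value as its goal and cites a methods source, the collection window is only two years, and a full economic plan may give a rate. Much of this stands: the effect over the documented window is small, and the five-year figure rests on a horizon the documents do not give. What does not stand is the appeal to an unseen plan. The article does not merely leave out a rate; it names the wrong operation.

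A reader might go further and infer that the rules deduct the comparator twice. The documents do not say so. Section 3.6.3.1 speaks of drawing comparisons and states no subtraction; 3.6.3.2 assigns removal of what would have happened anyway to a later step; and Box 1 deducts from the total quantity of the outcome, which most naturally means the gross change. What remains is an undefined base that one sentence can settle.

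A reader might also infer that benefits are multiplied by the number of outcomes. That needs complete overlap at equal value, which is a ceiling and not an estimate. Section 3.7.2 lets the team choose the most relevant outcomes for each stakeholder, and the Introduction treats loneliness and social isolation as distinct. Section 3.6.3 also argues for a broad multi-outcome framework, so replacing it with a single measure would be a preference, not a correction.

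Finally, a reader might conclude that the ratio is wrong by construction. Overlap and missing discounting raise it, a misapplied deadweight deduction would lower it, and no proxy values are given. That conclusion is out of reach.

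**Conclusion.** The main point holds. As written, 3.6.3.1 yields constant prices and not present value, and nothing else in the SROI text supplies time discounting, although Box 1 projects outcomes into later years. Benefits in the ratio for hypothesis 3.2(ii) are overstated by about 1% to 11% over one to two years and by at most about 22% over five years. These figures assume rates of 3% to 7%, costs at the start and drop-off of 0 to 50% a year; the five-year horizon is also assumed. It cannot be shown that the conclusion about exceeding 1 would change.

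Overlap between summed outcomes is a real risk whose size the documents do not determine. The base for deadweight is a point to clarify, not a demonstrated error. All of this concerns the economic component and leaves the primary loneliness outcome untouched.

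**What to change.** 1. In 3.6.3.1 and Box 1, separate the two operations: convert all costs and benefits to constant prices of a stated base year, then discount later-year costs and benefits at a stated annual rate. Report the ratio at a lower and a higher rate as sensitivity.
2. In 3.6.3.3, keep the planned sum and add a sensitivity ratio in which overlapping outcomes are counted once, with the rule for grouping them fixed before the ratio is calculated.
3. In Box 1, state that the comparator-based deadweight percentage is taken from the gross before-after change in the intervention group, and is not applied to a between-group difference.
4. In 3.6.3.2 and 3.6.3.3, use a word other than 'discounted' for the four SROI deductions, so that the term is kept for time.

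The cost is some rewording and modest extra analysis, with no new data. The reported ratio may be slightly less favourable.

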##### Establishing impact

3.6.3.2

This stage will determine those aspects of change that would have happened anyway or are a result of other factors. Such aspects will be eliminated from consideration. Qualitative and quantitative data (surveys on loneliness, social connection, depressive symptoms, wellbeing and quality of life at baseline, 3, 6 and 12 months) will provide this evidence. Monetised outcomes will be discounted on the basis of what would have happened without the intervention (deadweight), what outcomes are displaced by the intervention (displacement), who else has contributed to the outcomes aside from the funder (attribution), and whether experience of the outcomes declines over time (drop off).

##### Calculating the SROI

3.6.3.3

This will involve adding up all benefits. Investment into the *Connect Local* will be compared to the discounted, monetised value of benefits. The discounted, monetised value of benefits and outcomes will be divided by total investment (inputs) to estimate the SROI ratio.

#### Outcomes: implementation

3.6.4

In order to ascertain the effectiveness of the implementation of the program, the following methods will be used:

##### Reach and adoption

3.6.4.1

To ascertain the useability of the intervention (does it reach the right people? Are they using it?), we will collect demographic data of participants, number of clients who engage with the Community Connector and number of participants who complete the program, using administrative data from the *Connect Local* program, stored in Bolton Clarke’s client record system.

##### Feasibility, acceptability, and appropriateness

3.6.4.2

To ascertain the perceived fit and relevance of the intervention, the extent to which it can be used in the participating organisations, and acceptability (overall experience), we will collect: time taken to complete the program (collected through administrative data), perception/attitudes of all stakeholders as to the ease of use, usefulness of, and satisfaction with, the program (through interviews), and organisational support systems and processes also through interviews as well as the Resource Use Questionnaire [adapted from Fletcher et al. (65)] collected at 3, 6 and 12 months.

##### Fidelity and sustainability

3.6.4.3

To ascertain the uptake of the intervention into practice as planned, and the extent to which it can be embedded into practice to promote sustainability, we will use administrative data on the delivery of all four program components outlined in section 2.2 above, and organisational support systems and processes to enable this. We will supplement this information with in-depth data from interviews/focus groups with all participant groups, using open-ended questions around the participant experiences of the program components by participants. These questions will include sharing thoughts on: being made aware of the program and signing up; the engagement with the community connector – the process of finding out ‘what matters to you?’; How they connected with the programs/activities; Whether this went well and what happened then.

### Data analysis

3.7

#### Outcome 1: intervention evaluation – program effectiveness

3.7.1

##### Quantitative data analysis

3.7.1.1

For all quantitative, repeated, continuous individual level variables (loneliness, social isolation, social anxiety, depressive symptoms, wellbeing, quality of life) the main research question will be whether the study intervention is effective at improving the outcome of interest compared with usual care. Modelling these data will focus on fitting linear mixed models using different covariance matrices such as: unstructured, an exchangeable-changeable and AR level-1 residual matrices, where the mean structure of all fitted models include a term for intervention group and a term for time and an interaction term for time and intervention. Non-linear outcomes will be fitted using Generalised Estimating Equations (GEE) analysis which requires that the missingness mechanism is Missing Completely At Random (MCAR). Alternatively, polynomials and/or piecewise linear functions will be utilised for modelling outcomes with non-linear growth trajectories if responses are Missing At Random (MAR). To ascertain whether the missing data is MCAR or MAR, we will utilise methods such as data inspection, applying domain knowledge and comparing summary statistics between cases with complete data and those with missing data to determine the missing data mechanism. An understanding of the mechanism will enable an appropriate statistical method to be chosen to handle the missing values in the data set.

For quantitative, binary or dichotomous individual level outcomes (scales that have cut-off scores: loneliness (UCLA-3), social anxiety, depressive symptoms) additional analysis will be undertaken addressing the research question: do the interventions differ in their effectiveness, such that individuals in the intervention group experience a greater improvement in their probability of achieving the desired outcome compared to those receiving usual care. Generalised linear mixed models (GLMMs) for dichotomous outcomes will be used as well as GEE. The typology of missing data will be investigated to make sure that the assumptions of the adopted statistical technique are not violated. Our choice of GLMMs is based on the specific characteristics of the data, as well as the advantages provided by GLMMs in handling dependent responses in longitudinal or repeated measures studies. As highlighted in Breslow and Clayton (75), GLMMs incorporate random effects into the linear predictors and are particularly well-suited for modelling the dependence among response variables in such study designs.

Selection of the model that best fits the data will be based on the low goodness-of-fit measures such as the Akaike information criterion (AIC) and Bayesian information criterion (BIC). Additionally, the log-likelihood ratio test will be employed as another method for evaluating model fit.

All quantitative community and system level variables, as well as the goal attainment will be analysed descriptively. Descriptive statistics will be presented as proportions, means (standard deviations) or, for variables that did not conform to a normal or log-normal distribution, medians (interquartile range).

Statistical analysis will be performed using STATA V.15.0 (STATA Corp LP., College Station, Texas, United States). We will use a Type I error rate of 5% to indicate statistical significance, with 95% confidence intervals (CI).

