### Implementation: *Connect local* will be implemented as planned

3.3

The program effectiveness and cost-effectiveness components will be evaluated in a prospective, cohort quasi-experimental (non-randomised), pragmatic trial, using a convenience sample of participants, with the intervention group drawn from those living in the target LGA who access the community connector.

*Research question components using SPIDER:*

Sample: older community members, volunteers and service provider participants;

Phenomena of interest: reach, adoption, feasibility, appropriateness, fidelity, sustainability.

Design: prospective surveys, semi-structured interviews, administrative data;

Evaluation: implementation of program as planned;

Research type: mixed methods.

Question: What are the perceptions and experiences of [participants] about the *Connect Local* program and it being implemented as planned?

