### The intervention: *Connect Local*

3.4

The *Connect Local* program will involve eligible individuals to access a trained and paid Community Connecter professional. Community Connectors are individuals with a counselling, community development, health/allied health professional and/or life coaching background, who receive training in social prescribing (55), wellness and reablement and positive ageing, diversity in ageing, mental health first aid and trauma informed care.

Once a referral/contact is received, the *Connect Local* program manager contacts the community member and first discusses the program, to ascertain that it is what they are seeking. If so, the community member is screened for eligibility, namely, they live in target geographic location, are aged 65 or older, have a chronic health condition, and are in need of social connection. If appropriate, the program manager organises the Community Connector to contact the individual to organise a time to meet face to face and commence the program. As shown in Figure 3, the Community Connector will work with eligible community members to:

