**Figure 3 fig3:**
[figure not shown]
Service flow of *Connect Local*. Adapted from Mann et al. (20).

Individuals who participate in all four elements will be considered to have completed the full program. Meetings between the Community Connector and the participant will be undertaken in a mutually agreed upon location, including local community houses, local spaces such as libraries, local cafés, or in the participant’s home.

People will be engaged in the program through multiple sources: the local tertiary hospital, aged care provider, general practices, allied health providers, community health providers, through the program website, and general community access.

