#### Older community members: comparator

3.5.2

Given the proposed whole of community impact of *Connect Local* program, the inclusion criteria for the comparator group are the same as for the intervention group, except that they do not live in the target LGA. These participants will be recruited from the local tertiary hospital and aged and community care provider. All eligible individuals will be made aware of the program through their care provider and will be asked if their details can be shared with the researchers to contact them about the study. The researchers will contact the individuals to obtain consent. Recruitment will be monitored in blocks of five to match comparator participants by age and gender to the intervention participant group.

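### In a non-randomised comparison with different recruitment routes, the stated mixed models name only group, time and group-by-time, and the article names no confounder adjustment.

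*Protocol article*

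**What the plan says.** Section 3.3 describes a "prospective, cohort quasi-experimental (non-randomised), pragmatic trial, using a convenience sample of participants". It goes on to say how the treated arm arises: "with the intervention group drawn from those living in the target LGA who access the community connector".

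The two groups enter differently. Section 3.4 lists the intervention sources as "the local tertiary hospital, aged care provider, general practices, allied health providers, community health providers, through the program website, and general community access". Before eligibility screening, the program manager "first discusses the program, to ascertain that it is what they are seeking". For comparators, section 3.5.2 says: "These participants will be recruited from the local tertiary hospital and aged and community care provider". It describes no equivalent check that they want such help. Their inclusion criteria are "the same as for the intervention group, except that they do not live in the target LGA", and recruitment is monitored so that they match the intervention group on age and gender.

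For the repeated continuous outcomes, section 3.7.1.1 plans linear mixed models in which "the mean structure of all fitted models include a term for intervention group and a term for time and an interaction term"; the interaction meant is group-by-time. Covariance structure and model fit are judged by AIC, BIC and a likelihood ratio test. For the binary outcomes the section names GLMMs and GEE without giving their terms.

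Table 3 schedules demographic information, UCLA-3, GDS-5, LSNS-18, Mini-SPIN, WEMWBS, EQ-5D-5L and the resource use questionnaire at baseline. Section 1.2 says a conceptual model of loneliness guided the choice of variables. That model's risk factors include marital status, living situation, socioeconomic status and health.

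**The concern.** In a non-randomised comparison, the choice of adjustment variables largely decides whether the group contrast can be read as a program effect. Here the fixed effects are stated, and none of them is a confounder or a matching factor.

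The group-by-time term cancels a baseline difference that would have persisted unchanged. It does not cancel a difference in how the two groups would have changed without the program. Such differences are plausible. Eligibility in section 3.5.1 is through loneliness, isolation and/or depressive symptoms, so the groups may qualify in different proportions by each and start at different UCLA-3 levels. People recruited through a hospital may be recovering. People who approach a connection program may be ready to connect anyway. Age and gender matching addresses none of these directly.

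The primary UCLA-3 result is at stake. So is the economic evaluation, because Box 1 takes deadweight from the same comparator group.

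**Working it through.** **The plan's own figures.** Section 3.6.2.3.1 gives a 0.85-point reduction and an effect size of 0.37, so the implied SD is 0.85 / 0.37 = 2.30. The stated 76 matches a one-group calculation on change: (1.960 + 1.282)² / 0.37² = 76.75. I therefore read 2.30 as the SD of change. With 88 recruited per group and 15% attrition, 88 × 0.85 = 74.8, or about 75 per group at 3 months. The point about the model does not depend on the sample size.

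**Routes and control**

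| | Intervention | Comparator |
|---|---|---|
| Area | Target LGA | Other LGAs |
| Entry | Seven sources, including website and general community access | Hospital and care provider |
| Confirmed to be seeking the program | Yes | Not described |
| Control by design | Age and gender matching | Age and gender matching |
| Control in the stated model | None named | None named |

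**Illustration 1: regression to the mean.** Two assumptions come from outside the document: a baseline UCLA-3 gap of 1 point, and a within-group baseline-to-follow-up correlation r of 0.5 to 0.7 with equal variances. If both groups regress to a common mean and the program does nothing, the difference in change is (1 − r) × 1 in absolute value.

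- Standard error: 2.3 × √(2/75) = 0.376.
- r = 0.5: shift 0.5 points, 0.5 / 0.85 = 59% of target, 0.5 / 0.376 = 1.33 SE. The two-sided 5% test rejects with probability 26.5%.
- r = 0.7: shift 0.3 points, 0.3 / 0.85 = 35% of target, 0.3 / 0.376 = 0.80 SE. The rejection probability is 12.6%.

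Holding the SD of change at 2.3 implies a baseline SD of 2.3 / √(2(1 − r)), which is 2.30 at r = 0.5 and 2.97 at r = 0.7. The 1-point gap is then 0.43 or 0.34 of a baseline SD.

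**The same gap under the opposite assumption.** If the gap is stable, each group regresses to its own mean. The change contrast then has no such bias, while conditioning on baseline shifts the estimate by (1 − r) × 1 = 0.3 to 0.5 points. The two analyses rest on different assumptions, and the document does not show which holds.

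**Illustration 2: any omitted baseline factor.** Assume 76 per group, a between-group difference of 0.2 to 0.5 SD in the factor, and a correlation of 0.1 to 0.5 with change. Bias in SD units is the product, and SE = √(2/76) = 0.162 SD.

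| Difference (SD) | Correlation | Bias (points) | Share of 0.85 | Actual type I error |
|---|---|---|---|---|
| 0.2 | 0.1 | 0.05 | 5% | 5.2% |
| 0.3 | 0.3 | 0.21 | 24% | 8.6% |
| 0.5 | 0.5 | 0.57 | 68% | 33.8% |

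The range runs from negligible to large, and the document gives nothing with which to narrow it.

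**The case against.** The strongest reply is that the sentence says the models include these terms, which does not exclude others, and that a condensed article may leave a covariate list to the analysis plan. A reader might infer that every model contains only these three terms. The text does not support that: the sentence belongs to the linear mixed models, and no terms are given for the GLMM and GEE analyses. What remains is that the fixed effects were written down, none is a confounder, and no adjustment is mentioned anywhere in the article.

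A second reply is that the design already helps. The comparator is concurrent, eligibility is the same apart from area, age and gender are matched, and the contrast is in change. This is fair, and it reduces the problem. It does not deal with different expected trajectories.

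A third reply is that the bias figures are assumed. That is correct. A reader might infer that the 5% error rate is shown to fail. It is not shown: the 1-point gap appears nowhere in the document and is larger than the planned effect, the common-mean assumption may be wrong, and the low end of the second illustration is close to nominal.

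Finally, a reader might infer that every needed adjuster is already collected. Table 3 lists neither referral source nor motivation. Adjustment reaches measured factors only.

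**Conclusion.** The point holds in a limited form. The groups are not randomised, enter by different routes and are matched on two variables, while the stated mean structure for the linear mixed models names no confounder. Followed as written, the plan gives a primary estimate open to confounding of change, although relevant baseline measures are scheduled.

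The size and direction of the bias cannot be obtained from the document. The 0.3 to 0.5 point figure, with rejection rates of 12.6% to 26.5%, is conditional on the assumed 1-point gap, correlations of 0.5 to 0.7 and regression to a common mean. It shows that the problem could matter against a target of 0.85. It does not estimate what will happen.

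**What to change.** In section 3.7.1.1, make the primary analysis an adjusted mixed model of the 3-, 6- and 12-month UCLA-3 scores, with baseline removed from the response. Include group, time, group-by-time, baseline UCLA-3, baseline UCLA-3 by time, age, gender and a short prespecified set of baseline variables, for example living situation, GDS-5, LSNS-18, EQ-5D-5L and prior health-service use. Living situation is assumed to be part of the demographic information, which Table 3 does not itemise. Baseline must leave the response because it cannot be both outcome and covariate. If it stayed there, covariate main effects alone would leave the group-by-time contrast essentially unchanged.

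Add three sensitivity analyses:

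- The planned unadjusted change model, because it rests on a different assumption about the baseline gap.
- A propensity-score overlap-weighted analysis on the same variables.
- An analysis restricted to intervention participants referred by the hospital or aged care provider.

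Do not use referral source as a covariate, because most of its levels exist only in the intervention group. Do not use a willingness question put only to comparators, because it has no counterpart in the intervention group, where wanting the program is part of entry.

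The cost is mainly analysis wording. With one term for each example variable, the added covariate terms are 1 (baseline UCLA-3) + 2 (its interaction with time) + 2 (age, gender) + 5 = 10, for about 2 × 75 = 150 completers at 3 months. Participants with no follow-up score would not contribute to the adjusted model. The weighted and restricted analyses have a smaller effective sample, and the restricted one needs entry route recorded for intervention participants. Unmeasured motivation should be stated as a remaining limitation.
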